**Fig. 1 Fig1:**
[figure not shown]
Timeline of intervention and outcome measurements

Participants receive 10 treatment sessions of daily AIH or daily SHAM. A single AIH session consists of 15, 90s episodes of breathing at a fraction of inspired oxygen (FiO_2_) of 0.10 ± 0.02 with 60s intervals of 0.21 ± 0.02 FiO_2_ (room air). While a single daily SHAM session consists of 15, 90s episodes of 0.21 ± 0.02 FiO_2_ with 60s intervals of 0.21 ± 0.02 FiO_2_ (room air). We provide the treatments via a custom air delivery system; see [10, 23, 32–34] for details. In brief, the delivery system directs a known air mixture from either a pressure-swing absorption (PSA) system [HYP-123; Hypoxico Inc., USA] or a blower source to the non-rebreather facemask. For safety, oxygen concentration within the breathing circuit is continuously monitored [OM-25RME; Maxtec Inc]. Additionally, we continuously monitor blood oxygen saturation (SpO_2_) and heart rate (HR) at 1-s intervals, and blood pressure (BP) every 5th breathing interval using a MASIMO system [MASIMO rainbow SET, Irvine, CA].
C.Walking practice

Walking practice sessions immediately follow (within 10 min) the breathing intervention and last for 60 min. Walking practice involves intensive training in walking-related functional tasks using a skill-based training approach. Recent studies found skill-based walking practice is more consistent with community walking, providing meaningful gains in walking function after neurologic injury [35–37]. Task-based walking practice replicates environmental challenges encountered during real-world walking [36] and corresponds to gains in walking balance, speed, and endurance that can be measured using the timed-up and go (TUG), 10-m walk test (10MWT), and 6-min walk test (6MWT), respectively [37]. The walking practice incorporates activities to develop skills in 5 walking-related task domains: 1) walking balance (e.g., walking on different surfaces), 2) skilled walking (e.g., negotiating obstacles), 3) walking with a secondary task (e.g., walking and carrying object), 4) endurance, and 5) speed [37].

A licensed physical therapist with expertise in SCI locomotor training tailors all walking activities within each session to align with the participant’s walking ability, functional walking goals, and fatigue levels (Table 2). An overhead harness system (without provision of body weight support) is available to serve as a passive support during overground walking. Use of the harness allows participants to walk without fear of loss of balance or falling during walking practice with minimum use of hand-held walking aides. Each 60-min walking practice session is divided into two 25-min modules, involving [1] overground walking practice *with* harness support and minimum use of manual (therapist-provided) or physical (assistive device use, i.e. cane/walker/AFO) assistance, and [2] overground walking *without* harness support with use of an assistive device (if needed) by the participant and minimum use of manual assistance by the therapist. The training physical therapist ensures that participants take rest breaks as required (every 5–10 min) during training and also records SpO_2_, HR, and BP throughout the practice session.

**Table 2 Tab2:**
[figure not shown]
Summary of Aim 2 Experimental Groups

### Experimental protocol

D.Effects of dAIH on walking recovery in persons classified as non-ambulatory

We designed this protocol to examine if daily AIH improves walking recovery in persons with subacute SCI who are initially classified as non-ambulatory. Participants receive ten daily breathing sessions (5 days per week × 2 weeks) of either room air (daily SHAM) or daily AIH, while sitting comfortably in a chair or cushioned wheelchair. Each breathing session consists of 15 episodes of 90s hypoxia (0.10 ± 0.02 FiO_2_) for daily AIH or 90s normoxia (0.21 ± 0.02 FiO_2_; room air) for daily SHAM with 60s intervals of room air.
E.Effects of dAIH + WALK on walking recovery in persons classified as ambulatory

We designed this protocol to examine if daily AIH paired with task-specific, skilled, and intensive walking practice enhances walking recovery in persons with subacute SCI initially classified as ambulatory. Participants receive ten daily breathing sessions of either daily SHAM or daily AIH followed by daily 60-min walking practice (WALK). Our rationale is that daily AIH may be an effective pre-treatment for daily practice of walking skills, with the combined treatment being more powerful than either treatment alone, as seen in chronic SCI [10].

### Safety precautions

To ensure participant safety, we implement the following precautions:
A.*Protection against low oxygen risks during breathing sessions:* As moderate reductions in inspired oxygen may cause lightheadedness, dizziness, reduced vision, and/or euphoria, we continuously monitor SpO_2_, HR, and BP of all participants before, during, and after treatment and/or assessment sessions. If during a daily AIH treatment session a participant’s SpO_2_ levels fall below 70%, our AIH-delivery system is programmed to immediately switch from hypoxia to normal oxygen delivery (i.e. FiO2 = 0.21 O_2_) until the participant’s SpO_2_ levels re-saturate above 90%. Additionally, if participants exhibit any signs of lightheadedness, dizziness, reduced vision, and/or euphoria during a treatment session, we will immediately administer room air with our automated delivery system and the onsite study physician will conduct a clinical examination to assess if the participant should continue with treatment or terminate the session. Participants are able to discontinue treatment at any time for any reason.B.*Protection against fall risk during walking assessments and training:* We record each participant’s fall history and document any adverse events that may occur during their training or assessment visits. To ensure safety for all walking assessments, we allow participants to use an assistive device (AD) (e.g. cane, walker, crutches etc.) depending on their level of comfort and ambulatory status, while the assessing therapist and research assistants walk beside them. We also ensure that participants use the same AD for all assessments. To ensure participant safety during all walking-training sessions, the training physical therapist constantly monitors the participant and uses a gait belt if considered clinically necessary.C.*Protection against fatigue risk:* For all breathing sessions, we position participants in a comfortable seated or reclining position to minimize discomfort. During walking practice training, we ensure participants take seated or standing rest breaks every 5–10 min (or when requested) and between different modules. We resume training only after participants provide verbal confirmation that they are ready to continue. For all assessments, we continuously monitor participants for fatigue and balance instability, and ensure that they take frequent rest breaks (2–5 min) between different assessment tests.D.*Protection against cardiopulmonary risk:* The assigned physical therapist (with help from a research assistant) monitors cardiopulmonary vitals (i.e. HR, BP, and SpO_2_) pre and post all assessment and treatment sessions (breathing and walking training). If a participant reports any discomfort, the on-site clinician will stop the assessment/training session for a seated/standing break (depending on participant preferences) and monitor vitals to determine if the participant’s condition is stable enough to continue after a rest period or to terminate the session altogether. The onsite clinician can also immediately withdraw participants from the study in case of serious medical issues that may arise during treatment or assessment; for example, signs of autonomic dysreflexia, rapid change in heart rate or systolic blood pressure, diaphoresis, severe headache or dizziness. All clinical and research staff members are trained to provide First Aid and CPR in case of emergency. Additionally, if a participant gets ill or injured from being in our study, a medical team (present on site for all sessions) is available to attend to the participant. Participants can return to continuing the study only after they have received medical clearance from our study physician.

### Outcome measures

We provide a summary of primary and secondary outcomes measures in Table 3. We quantify overground walking ability using three primary measures: timed up-and-go test (TUG, walking initiation and balance), ten-meter walk test (10MWT, walking speed), and six-minute walk test (6MWT, walking endurance). These tests capture functional ambulation, exhibit high reliability and construct validity, and have precedence for quantifying and distinguishing degrees of functional ambulatory recovery post SCI [38–40]. In our previous study in persons with chronic SCI, we found these tests to be more sensitive to changes in walking function and functional ambulation compared to AIS grade or categorical ambulation metrics [41]. During all walking assessments, we use a 75-ft long walkway and allow participants to use their least restrictive hand-held assistive device of choice (if needed).

**Table 3 Tab3:**
[figure not shown]
Timeline for clinical assessments and outcome measurements

We ensure a minimum of 5-min for rest breaks between tests. Participants able to ambulate attempt two trials each for the TUG and 10MWT (at their fastest, but comfortable and safe speed) with a minimum of 1-min rest between trials. The average TUG time and 10MWT speed for the two the trials will be used for analyses. Participants will attempt a single trial of the 6MWT at their fastest yet comfortable walking speed that is sustainable for six minutes, while distance covered at 2 and 6-min time points is recorded. We quantify success of completing each of the tests using a recovery score of 0–3 (0 = complete, 1 = attempted test, 2 = partially recovered but failed to complete; 3 = fully recovered). We also record secondary outcome measures of walking function that include the Walking Index for Spinal Cord Injury (WISCI) II [42] and SCI Functional Ambulation Index (SCI-FAI) [43].

To quantify maladaptive changes that may potentially occur following daily AIH exposure, we measure the magnitude and frequency of pain, spasticity, systemic hypertension, and autonomic dysreflexia during our assessments.
Pain severity: Using the five-point Wong-Baker FACES scale of 0 (no pain) to 5 (extreme pain) [44, 45].Spasticity: Using the Spinal Cord Assessment Tool for Spastic Reflexes (SCATS) [46], and the cumulative sum of three SCATS subscales: clonus (0 = no spasticity; 3 = severe), flexor (0 = no spasticity; 3 = severe), and extensor (0 = no spasticity; 3 = severe); and spasms using the Penn Spasm Frequency Scale (PSFS) [47].Blood pressure: At all pre-post treatment/assessment and follow-up time points. For each participant we specifically record hypertension incident rate, i.e. number of hypertensive events divided by units of person-measures (the sum of the total number of BP measurements), which accounts for the total number of chances for detecting a hypertensive event and for measurements not made due to dropout or a disqualifying adverse event [48]. We will also compute relative risk for participants within each group, i.e. hypertension incidence rate in the daily AIH subgroup over that in the daily SHAM and/or WALK groups [49], respectively, with a relative risk of one indicating no association between systemic hypertension incidence with interventions.Autonomic dysreflexia incident rate i.e. number of autonomic dysreflexia events divided by the total person-time (number of study days completed by each participant) to account for the total number of chances for detecting autonomic dysreflexia for days not measured due to dropout or a disqualifying adverse event [48]. We also compute relative risk within each group, as autonomic dysreflexia incidence rate in the daily AIH group over the incidence rate in the daily SHAM and WALK groups, respectively [49].

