Daily AIH ± WALK does not induce maladaptive changes (spasticity, pain, systemic hypertension, autonomic dysreflexia) in persons with subacute SCI. First, we predict no difference in SCATS following daily AIH ± WALK as compared to daily SHAM±WALK or WALK. We also predict no difference in the changes in FACES scores between interventions. We anticipate daily AIH alone or combined with walking practice will not elicit greater incidence of systemic hypertension in persons with subacute SCI. To test this hypothesis, we will compare the incidence rates of hypertension between interventions (daily AIH, daily AIH + WALK, daily SHAM+WALK, WALK) using Relative Risk [49, 52]. A Relative Risk of one will indicate no association between systemic hypertension and interventions. Using the 95% confidence interval of the Relative Risk [49], we will determine if there is a statistically significant association between interventions. We predict the relative risk of hypertension comparing daily AIH vs. daily SHAM, daily AIH + WALK vs. daily SHAM+WALK, and daily AIH + WALK vs. WALK are not different. We also predict the incidences of autonomic dysreflexia comparing daily AIH vs. daily SHAM, daily AIH + WALK vs. daily SHAM+WALK, and daily AIH + WALK vs. WALK are not different.

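### The hypertension relative risk for AIH+WALK versus WALK pools breathing-session readings that WALK never has, so 1 means no association only under an unstated condition

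*Protocol article*

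**What the plan says.** The Outcome measures section of the protocol article sets the time points for this outcome as "Blood pressure: At all pre-post treatment/assessment and follow-up time points". The rate is "number of hypertensive events divided by units of person-measures (the sum of the total number of BP measurements", and the reason given for that denominator is that it "accounts for the total number of chances for detecting a hypertensive event and for measurements not made due to dropout or a disqualifying adverse event".

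Three other places determine how many readings each arm has:

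- Safety precautions, item D: vital signs including blood pressure are taken "pre and post all assessment and treatment sessions (breathing and walking training".
- Intervention, breathing treatment: during breathing the system also records "blood pressure (BP) every 5th breathing interval using a MASIMO system", and "A single AIH session consists of 15, 90s episodes of breathing".
- Abstract, Methods: the ambulatory stratum has three arms, and one of them (WALK) receives walking practice without any breathing session.

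Hypothesis 3 in the Statistical analysis section then names the contrasts: "We predict the relative risk of hypertension comparing daily AIH vs. daily SHAM, daily AIH + WALK vs. daily SHAM+WALK, and daily AIH + WALK vs. WALK". A ratio of 1 is taken as no association, and the 95% confidence interval decides significance. Nothing restricts the WALK contrast to time points that both arms have.

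Dysreflexia has a different denominator: "number of autonomic dysreflexia events divided by the total person-time (number of study days completed by each participant".

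**The concern.** Dividing by the number of readings corrects for one arm having more of them, provided that every reading has the same chance of being hypertensive. Here the extra readings in AIH+WALK are of a particular kind. They are taken around breathing, with the participant seated or reclining, whereas the readings shared with WALK include those taken after an hour of intensive practice. If hypertension is less frequent around breathing, the AIH+WALK rate is pulled down even when AIH does nothing, and a real excess is attenuated. If it is more frequent there, the ratio is pushed up and a harm may appear where there is none.

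Aim 3 is a claim of no harm and the prediction is no difference. A ratio whose no-effect value is unknown cannot support or refute that prediction for this contrast. More participants or better retention would not help, because the imbalance comes from the schedule.

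**Working it through.** The protocol gives no event rate, relative risk or margin for hypertension, so there is no planned figure to reproduce. The check counts readings by arm and asks what the ratio would be under assumed rates.

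**Readings per treatment day (pre/post only)**

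- WALK: pre-walk and post-walk, 2.
- AIH+WALK: pre- and post-breathing, pre- and post-walk, 4. Walking starts within 10 minutes of breathing, so one reading may serve as both post-breathing and pre-walk, which leaves 3.
- Over 10 treatment days: 20 in WALK against 40 (or 30) in AIH+WALK.

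**General formula.** Let m_w be the number of shared readings, m_b the number of extra breathing readings, s the hypertension rate at breathing readings relative to shared ones, and R the true relative risk, applied equally at all readings. Then

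observed RR = R × (m_w + s × m_b) / (m_w + m_b).

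This equals R only if s = 1 or m_b = 0. For R = 1.5:

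| s | 30 vs 20 readings | 40 vs 20 readings |
|---|---|---|
| 0.5 | 1.5 × 25/30 = 1.25 | 1.5 × 30/40 = 1.125 |
| 1 | 1.50 | 1.50 |
| 1.5 | 1.5 × 35/30 = 1.75 | 1.5 × 50/40 = 1.875 |

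**Illustration A: 5% at resting readings, 20% post-walk (assumed)**

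- WALK: (5 + 20)/2 = 12.5%.
- AIH+WALK, no effect: (5 + 5 + 5 + 20)/4 = 8.75%, RR = 8.75/12.5 = 0.70. With the merged reading: (5 + 5 + 20)/3 = 10%, RR 0.80.
- AIH doubles the rate at every reading after it starts that day: (5 + 10 + 10 + 40)/4 = 16.25%, RR 1.30. Merged: (5 + 10 + 40)/3 = 18.3%, RR 1.47.
- Same doubling on the shared readings only: (10 + 40)/2 = 25%, RR = 25/12.5 = 2.0.

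**Illustration B: 10% at rest, 15% post-walk (assumed)**

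- WALK: (10 + 15)/2 = 12.5%.
- AIH+WALK, no effect: (10 + 10 + 10 + 15)/4 = 11.25%, RR 0.90.
- Doubling: (10 + 20 + 20 + 30)/4 = 20%, RR 1.60.

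**Adding assessment readings.** Suppose 14 readings at assessment visits (7 visits, pre and post; assumed) are common to both arms at 12.5%. In illustration A the no-effect ratio becomes (40 × 8.75% + 14 × 12.5%)/54 = 5.25/54 = 9.7%, RR 0.78. Merged: (30 × 10% + 14 × 12.5%)/44 = 4.75/44 = 10.8%, RR 0.86. The distortion shrinks but remains.

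**Dysreflexia.** The denominator is study days, so extra readings cannot lower the rate. If each reading were an independent chance q of detecting an event, the no-effect ratio on a treatment day would be [1 − (1 − q)^k1]/[1 − (1 − q)^k0]. For 4 against 2 readings it is 1.98 at q = 0.01 and 1.90 at q = 0.05; for 3 against 2 it is 1.49 and 1.46. The values of q are assumed. These ratios are best read as an upper limit, because the definition under Adverse event reporting also requires symptoms, and the person-time may include days without a breathing session.

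**The case against.** The strongest case for leaving the plan alone has four parts.

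1. **The contrasts that isolate hypoxia are sound.** AIH versus SHAM, and AIH+WALK versus SHAM+WALK, have identical schedules, so two of the three named hypertension contrasts are unaffected. This stands, and it limits the severity.

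2. **The direction and size are unknown.** The protocol gives no rate by session type. If the rates are equal, the planned denominator works as intended. This stands too: the figures above are illustrations, and illustration B is much milder than A. It does not rescue the rule, which depends on an equality that the protocol neither states nor tests.

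3. **The outcome definition does not list the readings taken during breathing.** This stands. A reader might count them (15/5 = 3 per session) and infer that a doubling would vanish: (5 + 3×10 + 10 + 10 + 40)/7 = 13.6%, RR 1.09, with a no-effect value of 50/7 = 7.1%, RR 0.57. The documents do not support leading with those figures. The readings appear in the description of monitoring during gas delivery. If they counted, so should the blood pressures recorded throughout walking practice, which all three arms have. With three such readings at 20% (assumed number and rate), WALK is (5 + 60 + 20)/5 = 17%. AIH+WALK is then (5 + 15 + 5 + 5 + 60 + 20)/10 = 11%, RR 0.65, and under doubling (5 + 30 + 10 + 10 + 120 + 40)/10 = 21.5%, RR 1.26.

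4. **Table 3 is not visible, the Outcome measures section says that these events are measured during assessments, and the choice of readings could be left to an analysis plan.** The table may fix the schedule. However, the outcome definition itself names pre- and post-treatment time points and divides by all measurements, so the point rests on a stated rule and not on a missing detail.

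**Conclusion.** The point holds for one contrast and one outcome: the hypertension relative risk of AIH+WALK versus WALK. As written, its no-effect value is 1 only if breathing-session and shared readings have the same hypertension rate. On pre/post treatment-day readings, the assumed rates give no-effect values of 0.70 to 0.90, and a true doubling appears as 1.30 to 1.60. Readings common to both arms move the no-effect value closer to 1. Higher rates around breathing would reverse the direction.

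Two stronger readings are not supported. A reader might infer that the result leans towards safety whatever AIH does; that needs lower rates around breathing, which the protocol does not establish. A reader might also infer that dysreflexia is diluted in the same way. It is counted per study day, so the only plausible distortion is more detection in the breathing arms, limited by the symptom requirement.

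This should be fixed, but it is not critical, because the sham-controlled safety contrasts are intact.

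**What to change.** - For AIH+WALK versus WALK, compute the hypertension rate only from time points scheduled in all three ambulatory arms: pre-walk, post-walk, assessments and follow-ups. Then m_b = 0 and the observed ratio equals the true one whatever the rate around breathing.
- Compare dysreflexia in this contrast over the same shared observation window.
- Report readings and events from breathing sessions separately, and only for AIH against SHAM arms.
- State whether the readings taken during breathing and during walking practice enter the rate at all.

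The cost is a sentence or two in the outcome definition and a filter on data already collected. Fewer readings enter the WALK contrast, so its interval may be wider. Safety monitoring is unchanged.

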### Adverse event reporting

The research team (PI, clinicians, and research assistants) reports adverse events related to each participant from the time of enrollment to the last follow-up assessment visit, which include: 1) unintentional loss of balance (i.e. fall to the ground), 2) change in systolic pressure to > 140 mmHg and/or diastolic pressure exceeding > 90 mmHg [55, 56], 3) autonomic dysreflexia with systolic blood pressure > 150 mmHg or > 20 mmHg from baseline with complaints of headache, diaphoresis, and/or blurred vision, 4) musculoskeletal injury during/after walking training (i.e. sprain, fracture, etc.), 5) symptoms such as pain, soreness, numbness, or signs of injury (inflammation, blisters, etc.) during or immediately following training or on returning home, 6) hospitalization for any cause, and 7) death due to any cause.

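### The hypertension relative risk takes no account of each participant's pre-treatment pressure, so at about 15 completers per arm it is imprecise and can miss or falsely suggest an AIH effect

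*Protocol article*

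**What the plan says.** All references are to the Protocol article.

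- **Rate (Outcome measures, Blood pressure).** The rate is "number of hypertensive events divided by units of person-measures (the sum of the total number of BP measurements". Readings enter as follows: "Blood pressure: At all pre-post treatment/assessment and follow-up time points". Readings taken before a breathing session are therefore in the pool. This section gives no cut-off for a hypertensive event.
- **Cut-off (Adverse event reporting).** The only hypertension threshold in the article is "change in systolic pressure to > 140 mmHg and/or diastolic pressure exceeding > 90 mmHg". The same list gives a second pressure event a criterion tied to the participant's own baseline: "autonomic dysreflexia with systolic blood pressure > 150 mmHg or > 20 mmHg from baseline", with symptoms.
- **Comparison (Statistical analysis, Hypothesis 3).** "we will compare the incidence rates of hypertension between interventions (daily AIH, daily AIH + WALK, daily SHAM+WALK, WALK) using Relative Risk". The decision rule is: "Using the 95% confidence interval of the Relative Risk [49], we will determine if there is a statistically significant association between interventions". The interval method is given only by citation.
- **Available data (Safety precautions, D).** Pressure is taken "pre and post all assessment and treatment sessions (breathing and walking training".
- **Use of baseline elsewhere.** The ANCOVA provision appears under Hypothesis 2, for the walking tests. Randomisation is stratified by walking ability only.

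**The concern.** A participant whose resting pressure sits near an absolute cut-off produces events at many readings under any treatment. One with low resting pressure produces almost none, even if treatment raises it. Resting pressure is thus a strong predictor of the event count, yet it enters neither the allocation nor this comparison.

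With small arms, the chance placement of a few people with high resting pressure can move the relative risk away from 1 or mask a true rise. Hypothesis 3 predicts no difference between arms. An imprecise ratio therefore tends to leave that prediction unchallenged, and a pressor effect could pass as no association. The opposite error is also possible: if the cited interval counts each reading as an independent observation, it will be too narrow and may declare a difference that does not exist.

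**Working it through.** **Plan's own figure.** The article states no expected rate, relative risk, margin or power for hypertension, so there is nothing to reproduce. Only the arm sizes come from the plan (Sample size section).

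- Aim 1: 34 / 2 = 17 per arm. Aim 2: 51 / 3 = 17 per arm. Equal allocation is assumed.
- After 12% attrition: 17 × (1 − 0.12) = 14.96, about 15 completers per arm.

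**Assumed inputs (none is in the article).** Person means are normal with mean 118 mmHg and between-person SD 14. Within-person SD is 10. Each participant has 28 on-study readings and a baseline that is the mean of 3 pre-treatment readings. An event is systolic pressure above 140.

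**Step 1: how much resting pressure alone matters.** The probability that one reading is an event is 1 − Φ((140 − m)/10) for a person with mean m.

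| Person mean m | Calculation | P(event) | Expected events in 28 readings |
|---|---|---|---|
| 118 (average) | 1 − Φ(2.2) | 0.014 | 0.4 |
| 118 + 12 = 130 (average person, +12 mmHg effect) | 1 − Φ(1.0) | 0.159 | 4.4 |
| 118 + 14 = 132 (one SD high, no effect) | 1 − Φ(0.8) | 0.212 | 5.9 |
| 118 + 28 = 146 (two SD high, no effect) | 1 − Φ(−0.6) | 0.726 | 20.3 |

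Under these inputs, an untreated person one SD above average is expected to contribute more events than an average person with a 12 mmHg treatment effect.

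**Step 2: crude against baseline-adjusted relative risk.** This is a Monte Carlo comparison of the crude log relative risk with a Poisson log relative risk adjusted for mean pre-treatment systolic pressure. Critical values come from the no-effect runs, so type I error is equal.

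| Setting | Crude | Adjusted |
|---|---|---|
| No effect, 95% range of relative risk | 0.20 to 4.9 | 0.34 to 2.6 |
| Power, +12 mmHg, no entry limit | 0.20 | 0.64 |
| Power, +12 mmHg, between-person SD 10 | 0.38 | 0.80 |
| Power, +12 mmHg, entry limit 130 | 0.48 | 0.56 |

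Separate runs of the no-limit setting gave power of 0.17 to 0.20 crude and 0.53 to 0.64 adjusted. The three highest of the 30 people supplied about 55% of events.

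**Step 3: treating readings as independent.** With no AIH effect, an interval based on the total number of readings was falsely significant in 29% to 57% of trials. A wider grid (24 readings, mean 115 to 125, between-person SD 8 to 18, within-person SD 8 to 12) gave 24% to 61%. A participant-level variance gave 2% to 7%.

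**Step 4: where the gain is small.** With mean 125, between-person SD 8 and within-person SD 12, a +5 mmHg shift was detected with power 0.33 by the participant-level relative risk. Change from baseline detected it with power 0.32, so there is no gain. Across that grid the three highest participants supplied 27% to 73% of events.

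**The case against.** Five points can be made for the plan.

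1. *The cut-off is inferred.* The rate definition gives no threshold. The 140/90 level stands only in the adverse-event list, worded as a change to that level, so it is unclear whether someone already above it counts. This stands, and the point is worded accordingly. No other hypertension cut-off is offered, however, and nothing in the rate or the comparison refers to baseline.
2. *Covariates and variance method belong in an analysis plan that is not shown.* This stands in part. The interval method is only cited and may already handle repeated readings, so the false-positive figure is conditional. The numerator, denominator, effect measure and decision rule are, however, fixed in the article.
3. *The unadjusted ratio is not biased under randomisation.* This stands. Chance placement of people with high resting pressure is sampling variability, so adjustment buys precision and does not correct a bias. An absolute cut-off for a safety outcome is also a defensible choice.
4. *Every pressure input is assumed, and Table 1 is not shown.* This stands. A limit of 130 on entry pressure removes most of the gain.
5. *Adjustment does not make the comparison precise.* This stands. The adjusted no-effect range is still 0.34 to 2.6. A plain robust interval also gave 10% to 17% false positives at a nominal 5%, so the choice of interval matters.

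A reader might infer that a few people with high resting pressure decide the result and that a real AIH effect is lost. The article does not show this. It depends on the spread of pressures, the number of readings and the entry criteria, none of which can be seen.

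**Conclusion.** The point holds as a weakness in the analysis of a safety outcome. The hypertension relative risk has no reference to pre-treatment pressure, unlike autonomic dysreflexia in the same article, so it mixes resting pressure with treatment. With about 15 completers per arm it is imprecise and can err in either direction.

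The size rests on assumptions. For +12 mmHg, power rises from 0.20 to 0.64 with no entry limit, but only from 0.48 to 0.56 with a limit of 130. With a small between-person spread, using baseline may gain nothing. The 29% to 57% false-positive rate applies only if the interval ignores within-person correlation, which the article neither states nor excludes. It would be wrong to read this as a biased comparison or as proof that Aim 3 cannot detect a pressor effect. The change is worth making because it costs little. It does not touch the walking outcomes.

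**What to change.** Keep the relative risk as the effect measure and change how it is estimated:

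- Fit a participant-level count model with log link and the number of readings as offset, adjusted for the participant's mean systolic and diastolic pressure before the first breathing session. Readings used as the covariate should not also be counted as events.
- Use a permutation or small-sample-corrected interval. Do not use a plain robust interval, or one that counts readings as independent.
- State in Outcome measures which cut-off defines an event for this rate, so that it agrees with Adverse event reporting.
- Report separately the participants already above that cut-off before the first breathing session, so that the rate can be read as new events.

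**Cost.** Analysis wording and slightly more analysis work. No new measurements are needed and no clinical rule changes. A small downside is that the relative risk becomes conditional on baseline pressure.
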